#### Analysis of endpoints

DFS will be calculated from date of randomization until date of death (from any cause), relapse or diagnosis of a SMN (whichever occurs first). Patients without an event will be censored at the date last seen. Analyses will be by intention-to-treat, with patients only excluded if they are later found to have been ineligible at randomization. The Kaplan-Meier method will be used for estimation of the 5-year DFS. The hazard ratio comparing DFS between the two treatment arms will be calculated from a Cox proportional hazards regression model and equality of hazards assessed with a Wald test, if the proportional hazards assumption is not violated. The Cox model will include the stratification variables used in the minimization: country, sex, age, WBC at diagnosis, MRD and genetic risk (high-risk genetic changes, TEL/AML1, high hyperdiploidy, B-other). The assumption of proportional hazards will be assessed using Schoenfeld residuals, and if violated the primary analysis will report the varying hazard ratio over the follow-up time along with their 95% confidence intervals.

The secondary endpoints will be measured from the date of randomization until date of event of interest and estimated using the Aalen-Johansen estimator. Differences for the randomized arms will be compared using Gray’s test. Patients who have not experienced the event of interest at the time of analysis will be censored at the date last seen, and the alternative secondary endpoints will be considered competing events. OS will be analysed using Cox regression and the Kaplan-Meier method will be used for estimation of 5-year OS.

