### Endpoints

#### Main study endpoint

5-year probability of DFS by intention-to-treat analysis.

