### Safety reporting

#### Temporary halt for reasons of subject safety

The sponsor will suspend the study if there is sufficient ground that continuation of the study will jeopardize subject health or safety. The sponsor will notify the accredited regulatory authorities (ethical committee, medicine agency) without undue delay of a temporary halt including the reason for such an action. The study will be suspended pending a further positive decision by the accredited regulatory authorities. The investigator will make sure that all subjects are informed.

An interim report will be prepared and submitted to the DSMB once a year. The potential risk of SOS will be balanced against DFS. The former develops during therapy, whereas most relapses and SMNs emerges after the end of therapy. Since the proportional reduction in relapse rate is anticipated to be ~ 50%, the acceptable risk of SOS is set to 3%. If a patient develops SOS on the standard MTX/6MP arm, the local physician will decide whether the standard MTX/6MP therapy regimen can continue.

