#### Outcome assumptions

The TEAM- and InO sub-protocols (that run in parallel) are regarded as fully independent experiments. For each of the two studies the outcome of the experimental intervention will be compared to the control arm, but comparisons between the two experimental arms will not be made. The patient numbers and power calculations are based on:United Kingdom will not provide patients to the TEAM study.French centers will join the ALLTogether1 protocol from October 2021.There will be an 80% participation rate of all eligible patients for the TEAM study.Patient accrual will be uniform over the 5 years accrual period.24% of randomized patients have T-ALL.50% are randomized to the experimental TEAM for both T- and BCP-ALL.The 5-years DFS for control BCP-ALL patients is 84% and for T-cell ALL it is 81%.

The primary endpoint is DFS, where we aim to show an improvement in the 5-year rate from 84 to 91% for BCP-patients (HR 0.54) and 81 to 87% (HR 0.61) for T-cell ALL compared to standard maintenance. A minimum of 778 randomized patients would be appropriate to assess this improvement with 80% power and a 2-sided 5% alpha. With 878 patients recruited over 5 years (assuming 39% are IR-high and 80% accept randomization), an additional 5 years follow-up, a 2-sided 5% alpha we will have 84% power to detect this difference.

Recruitment into R3 – TEAM will be discontinued after 778 patients have been randomized and found to be evaluable. Since power has been calculated for a 5-year recruitment time and a minimum of 2 years follow-up time for the last recruited patient, the follow-up time will be extended if the recruitment time is significantly shorter than 5 years.

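### The only between-arm test of DFS is dropped if proportional hazards is judged violated, and nothing with a decision rule takes its place

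*Protocol article*

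**What the plan says.** All references are to the protocol article.

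- **Main study endpoint:** "5-year probability of DFS by intention-to-treat analysis".
- **Outcome assumptions:** the primary endpoint is DFS. The target is 84% to 91% at 5 years in BCP-ALL and 81% to 87% in T-ALL, with 778 patients, 80% power and a 2-sided 5% alpha.
- **Analysis of endpoints, estimation:** "The Kaplan-Meier method will be used for estimation of the 5-year DFS". This carries no condition, and no between-arm comparison is attached to it.
- **Analysis of endpoints, test:** the hazard ratio comes from a Cox model that includes the minimization variables, with "equality of hazards assessed with a Wald test, if the proportional hazards assumption is not violated".
- **Analysis of endpoints, gate:** "The assumption of proportional hazards will be assessed using Schoenfeld residuals". No significance level or other threshold is given.
- **Analysis of endpoints, other branch:** "if violated the primary analysis will report the varying hazard ratio over the follow-up time along with their 95% confidence intervals". No test, time split, deciding interval or success criterion is named.

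**The concern.** The sample size section promises one test at a stated alpha and power. The analysis section makes that test conditional on a diagnostic computed from the same data, and the alternative branch is descriptive. If the diagnostic fails, a 778-patient phase 3 trial has no pre-specified answer to whether TEAM improved DFS. Any test chosen at that stage would be chosen after the curves had been seen.

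This is not a detail left to an analysis plan that is not shown. The article states the rule for the primary analysis in both branches, and an analysis plan that follows it inherits the gap.

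The fallback branch could be reached in practice. 6TG starts at 2.5 mg/m²/day and rises in 2-week steps of 2.5 to a maximum of 12.5, so reaching the maximum takes at least 4 × 2 = 8 weeks. Randomized therapy runs from week 37 to week 108, which is (108 − 37)/52 = 1.37 years, while follow-up lasts several years more. An effect that is not constant over that time is possible, though nothing in the article establishes it.

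**Working it through.** **1. Inputs.** From Outcome assumptions: 24% T-ALL, 1:1 allocation, uniform accrual over 5 years, and the 5-year DFS rates above.

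- Control: 0.76 × 0.84 + 0.24 × 0.81 = 0.8328
- TEAM: 0.76 × 0.91 + 0.24 × 0.87 = 0.9004
- HR = ln 0.9004 / ln 0.8328 = 0.573
- Control hazard = −ln 0.8328 / 5 = 0.0366 per year

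**2. Reproducing the stated power.**

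- Two proportions, 389 per arm: pooled SE under no difference = √(2 × 0.8666 × 0.1334 / 389) = 0.02438. SE under the alternative = √((0.8328 × 0.1672 + 0.9004 × 0.0996) / 389) = 0.02426. Then (0.0676 − 1.96 × 0.02438) / 0.02426 = 0.817, so power is 79.3% (stated: 80%). The same formula with 878 patients gives 83.9% (stated: 84%).
- Schoenfeld formula: events by 5 years = 389 × (0.1672 + 0.0996) = 103.8. Then √(103.8/4) × |ln 0.573| − 1.96 = 0.87, so power is 80.9%.

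The stated figures therefore describe an unconditional test.

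**3. Cost of the gate when hazards are proportional.** Simulation with exponential control DFS, an unadjusted Cox model, and a Schoenfeld-residual test on event rank. The 5% level for that test is assumed. A trial counts as a success only if the check passes and the Wald test is significant.

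| Setting (HR 0.573) | Wald test always done | Wald test through the gate |
|---|---|---|
| 778, every patient followed 5 years | 79.0% | 75.3% |
| 878, every patient followed 5 years | 84.3% | 79.6% |
| 778, 5-year accrual + 2 years | 74% | 70% |
| 778, 5-year accrual + 4.35 years | 89% | 85% |

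The check fails in about 5% of these trials, as a 5% test must. The loss is about 4 to 5 points (for example 79.0 − 75.3 = 3.7 and 84.3 − 79.6 = 4.7). The 4.35 years is roughly 5 years from end of induction, less the 8 months or so between end of induction and randomization.

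**4. Cost under assumed delayed effects.** 778 patients, 5-year accrual; each shape gives a 5-year DFS of about 90% on TEAM.

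| Assumed hazard ratio over time | Check fails (+2 or +4.35 years) |
|---|---|
| 1 for 8 weeks, then 0.56 | 5.5–5.9% |
| 0.7 on therapy, 0.52 after | 9% |
| 0.8 on therapy, 0.47 after | 17–18% |
| 1 for 1.37 years, then 0.41 | about 41–44% |

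In the last row, power is 69% ungated against 40% through the planned test at +2 years, and 94% against 54% at +4.35 years. In a close variant (HR 1 to 1.4 years, then 0.40, every patient followed 5 years) the check fails in 45.7% of trials, and power is 78.6% against 43.5%.

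**5. Type I error.** With no true effect and the fallback branch counted as making no claim, which is how it is written, the rate is 4.5% gated against 4.7% ungated (every patient followed 5 years). With staggered accrual the gated rate is about 4.6–4.8%. If instead a reader declared success whenever either of two period-specific 95% CIs excluded 1 after the check failed, the rate would be 8.0% (information split 50:50) or 8.1% (35:65).

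**The case against.** Four points can be made for the plan, and each limits the concern.

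**Alpha.** A reader might infer that the two-stage rule breaks the 5% level. The document does not support that. The roughly 8% figure needs a rule that either interval may decide, and the article says only that the varying hazard ratio will be reported. As written, the fallback claims nothing, so the error rate stays just under 5%.

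**Late effect.** A reader might take the safety section's remark, "The former develops during therapy, whereas most relapses and SMNs emerges after the end of therapy", as a sign that the treatment effect is delayed. It describes when events occur, in a paragraph about weighing SOS against DFS. Late events in both arms are compatible with proportional hazards. The 43% scenario also needs no effect at all during about 16 months of active treatment and a large one from the moment it stops. With only the 8-week titration lag, the check fails at close to its nominal rate.

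**Estimation.** It would be wrong to say that the fallback leaves nothing but time-varying hazard ratios. Kaplan-Meier 5-year DFS is estimated unconditionally. What is missing is a comparison.

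**Choice of test.** A reader might also object that the 5-year probability is never itself tested. Outcome assumptions names DFS as the primary endpoint and expresses the target as hazard ratios, so a Cox test of DFS is a conventional choice. Preferring a test at 5 years is a matter of taste, not a defect.

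The level of the check and the form of the time-varying model may well be settled in the analysis plan. None of this supplies a test for the branch in which the Wald test is not done.

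**Conclusion.** The point stands: one branch of the stated primary analysis has no between-arm test and no success rule, which is inconsistent with a trial powered for a 2-sided 5% test.

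Its size depends on the assumed 5% check. Under the design's own proportional hazards, the test is lost in about 5% of trials and about 4 to 5 points of power go with it. This part requires no delayed effect. Under delayed effects the check fails in about 6% (8-week lag), 9–18% (weaker effect on therapy) or about 43% (no effect until therapy ends) of trials. The last is an extreme of the range and not a forecast.

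The harm is lost power and an undefined decision. It is not a false-positive rate above 5%. The figures also rest on exponential control hazards, a blended BCP/T-ALL population and an unadjusted Cox model.

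**What to change.** Name one confirmatory test of DFS at 2-sided 5%, carried out whatever the Schoenfeld check shows. The covariate-adjusted Cox Wald test already planned would serve, as would a stratified log-rank test. Make the Schoenfeld check and any time-varying or period-specific hazard ratios supportive, with a sentence saying that they do not decide success. Add the between-arm difference in Kaplan-Meier 5-year DFS with its 95% CI, so that the named main endpoint is compared as well as estimated.

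The cost is one paragraph of protocol and analysis-plan wording, with no extra patients or data. It should be settled before outcomes are compared by arm. The downside is one of interpretation: if hazards are not proportional, the single hazard ratio is read as an average over the observed follow-up.

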#### Secondary study endpoints

OS by intention-to-treat (including association with DNA-TG).Association of DFS with DNA-TG.Risk of relapse (including association with DNA-TG). Here death in first complete remission (DCR1) and SMN will be analyzed as competing events.Risk of SMN (including association with DNA-TG). Here DCR1 and relapse will be analyzed as competing events.Cumulative incidence of SOS and NRH.Cumulative incidence of osteonecrosis.

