#### Randomization and treatment allocation

Screening is only allowed after written informed consent and can start 1–2 weeks after start of the last high-dose MTX in consolidation III. Screening after 2 weeks is preferred to prevent screening failures because of increased ALT, bilirubin or creatinine after high-dose MTX. 6MP will be stopped 2 weeks after start of HD-MTX. After screening, patients can be randomized as soon as they meet the inclusion criteria and do not meet any exclusion criteria.

Randomization will be using minimization stratified by: country, sex, age, WBC, immunophenotype, MRD and genetic risk (high-risk genetic changes, TEL/AML1, high hyperdiploidy, B-other).
During the study (i.e., until all randomized patients are off therapy), the randomization code will be broken to the study statistician to provide the annual progress report to the Data and Safety Monitoring Board (DSMB).

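### Relapse, the endpoint through which the trial expects its effect, is compared by Gray's test with no strata or covariates named, although allocation is minimized on prognostic factors that the primary analysis adjusts for

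*Protocol article*

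**What the plan says.** All references are to the protocol article.

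- **Allocation** (Randomization and treatment allocation): "Randomization will be using minimization stratified by: country, sex, age, WBC, immunophenotype, MRD and genetic risk".
- **Primary analysis** (Analysis of endpoints): "The Cox model will include the stratification variables used in the minimization: country, sex, age, WBC at diagnosis, MRD and genetic risk". That list leaves out immunophenotype, which is a separate matter and not relied on here.
- **Secondary cumulative-incidence endpoints** (same section, next paragraph): "estimated using the Aalen-Johansen estimator", then "Differences for the randomized arms will be compared using" Gray's test. No strata, covariates or regression model are named.
- **Relapse** (Secondary study endpoints): "Here death in first complete remission (DCR1) and SMN will be analyzed as competing events".
- **Overall survival**, also secondary: "OS will be analysed using Cox regression and the Kaplan-Meier method will be used for estimation of 5-year OS".

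The Abstract and the Discussion expect the DFS gain to come from halving the relapse rate. The Background expects death in remission and second malignancy to be equal between arms. Relapse is therefore the endpoint on which the trial's mechanism is tested.

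**The concern.** Minimization makes the arms more alike on prognostic factors than chance would. A test that ignores those factors computes its variance as if chance imbalance were still present. The variance is then too large and the test rejects less often than its nominal level.

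A second loss is independent of the allocation method. In time-to-event data, leaving out strong prognostic factors pulls the arm contrast towards the null and costs power.

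Two practical matters follow. DFS and relapse share most of their events but would be tested on different footings, so results near the threshold could differ because of adjustment alone. Also, Gray's test gives a p-value but no effect estimate to set against the assumed 50% reduction. The variables needed are already collected and already used for DFS.

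**Working it through.** **1. The plan's own power figure (DFS).** Inputs from Outcome assumptions: 24% T-ALL, control 5-year DFS 84% (BCP) and 81% (T-ALL), experimental 91% and 87%, two-sided 5%, equal allocation.

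- Blended control: 0.76 × 84 + 0.24 × 81 = 83.28%.
- Blended experimental: 0.76 × 91 + 0.24 × 87 = 90.04%.
- A two-proportion test gives 79.3% power at 389 per arm (778 in all; stated 80%) and 83.9% at 439 per arm (878; stated 84%).

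The stated figures reproduce. They concern DFS; the article states no power or alpha for any secondary endpoint.

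**2. Simulation set-up for relapse.** From the document: 778 patients, seven minimization factors, 5 years of accrual with at least 2 years of follow-up (so 2 to 7 years), and a relapse hazard ratio of 0.5. Assumed, because the document does not give them:

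- a biasing probability of 0.8;
- 13.5% control relapse at 5 years plus about 2.5% competing events (13.5 + 2.5 = 16%, matching 84% DFS);
- the prognostic strength of the factors, expressed as the standard deviation (SD) of the log hazard across patients.

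For scale, patients one SD above and one SD below the mean differ in hazard by exp(2 × SD). That is 2.6-fold at SD 0.47, 4.9-fold at 0.79 and 12-fold at 1.25.

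Unstratified Gray's test (a subdistribution log-rank) was compared with a Fine-Gray-type Wald test adjusted for all seven factors.

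**3. Results under minimization.** Size comes from 10,000 runs (3,000 at SD 0), power from 3,000 runs.

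| SD | Size, Gray | Size, adjusted | Power, Gray | Power, adjusted | Gain (points) |
|---|---|---|---|---|---|
| 0 | 5.2% | 5.5% | 79.60% | 79.17% | −0.43 |
| 0.47 | 4.4% | 5.0% | 80.57% | 81.03% | +0.46 |
| 0.79 | 4.3% | 5.4% | 76.60% | 79.10% | +2.50 |
| 1.25 | 3.5% | 5.5% | 71.23% | 79.43% | +8.20 |

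The Monte Carlo standard error of size is √(0.05 × 0.95 / 10,000) = 0.22 points. Separate runs of 3,000 (standard error 0.40 points) gave Gray sizes of 4.9, 4.9 and 3.8% at the three non-zero SDs. These are somewhat nearer nominal, but compatible.

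As a check, if the null z-statistic has standard deviation s, the size is 2 × [1 − Φ(1.96/s)]. The observed s of 0.975, 0.964 and 0.925 give 4.4, 4.2 and 3.4%, which agrees with the table.

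**4. Which loss comes from minimization?** Under simple randomization (3,000 runs), Gray's size was 4.6, 4.1, 4.9 and 5.1% for SD 0 to 1.25, with no downward trend. Power, Gray versus adjusted, was 77.63 versus 80.97% at SD 0.79 and 70.53 versus 79.33% at SD 1.25. The power gap is about the same as under minimization. Only the below-nominal size comes from minimization.

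**5. A second simulation with other assumptions.** Settings: MRD hazard ratio 1.6 to 2.5, high-risk genetics 1.9 to 3.2, biasing probability 0.85, 1,200 runs. Unadjusted size was 3.3 to 4.2%, and the gain at hazard ratio 0.5 was 0.5 to 2.3 points. The direction agrees. With 1,200 runs the standard error of size is about 0.6 points.

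**6. Subdistribution or cause-specific scale.** With so few competing events the choice hardly matters. At SD 0.79 under minimization, power was 76.60% for Gray's test and 76.73% for the cause-specific log-rank.

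**The case against.** The strongest reply is that lack of adjustment is inferred from silence. The article does not call Gray's test unstratified, Gray's test can be stratified, and an unseen analysis plan may do so. That limits how firmly the point can be put. It does not remove it: the section spells out covariates for DFS and, in the next paragraph, fixes a named test for the other endpoints with none.

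The other objections largely stand and set the size of the point:

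- The document gives no hazard ratios for the factors within the IR-high group, so the magnitude rests on assumptions. The Background does say that immunophenotype, genetics, white cell count and MRD correlate with cure, so zero effect is not the sponsor's own view.
- Aalen-Johansen curves with Gray's test are a coherent, standard pairing.
- Full adjustment, with 13 countries among the factors, took 22 parameters on about 92 relapses. The adjusted test's size was 5.0 to 5.5%, so part of its apparent gain is slight inflation.

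A reader might infer more than the documents support:

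- *That all secondary endpoints are affected.* Overall survival uses Cox regression, with covariates not excluded, and the DNA-TG associations are not arm comparisons.
- *That minimization causes the power loss.* Step 4 shows that it does not.
- *That the relapse test is invalid.* A conservative test does not create excess false positives.

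**Conclusion.** The point holds as a modest inefficiency in the test of the main explanatory endpoint. As written, the relapse comparison is valid but mildly conservative under minimization, with size about 3.5 to 4.4% at nominal 5%. Omitting the covariates costs about 0 to 3 points of power at hazard ratio 0.5 for weak to moderate factors, and about 8 points only for very strong ones. These figures depend on the assumed prognostic effects, event rates and biasing probability. The adjusted comparator used all seven factors; a shorter list was not simulated and recovers only the share of the gain that its factors carry. The primary DFS result is untouched, and no promise about relapse power is broken.

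**What to change.** For relapse, specify one of the following before outcome data are seen:

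- Gray's test stratified by a few main minimization factors, for example immunophenotype and MRD; or
- a test of the arm effect in a Fine-Gray or cause-specific Cox model with the main prognostic minimization factors, without all 13 countries as separate terms, reporting the hazard ratio and its confidence interval.

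Keep the Aalen-Johansen curves for display. Keep simple Gray's test for rare endpoints (second malignancy, SOS, NRH), where adjustment is unworkable. No change is asked for overall survival.

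The cost is a sentence or two of wording; the variables are already in the database. There are two small downsides. A regression model adds a proportional-hazards assumption. The covariate list must also stay short to avoid slight type I inflation, because relapses are few: 92 to 93 with no effect and 69 to 73 at hazard ratio 0.5 in the main simulation, and 99 to 112 with the effect present in the second.

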Sinusoidal obstruction syndrome (SOS): In case of persistent discordant thrombocytopenia < 75 × 10^9^/L (i.e., not accompanied by neutropenia < 0.75 × 10^9^/L) or any of the other clinical indications of SOS, the patient should be evaluated for SOS, incl. abdominal ultrasound, to determine the presence of ascites, reduced liver vessel flow, hepatic steatosis or fibrosis. The true incidence of SOS during 6MP/MTX therapy combined with very low dose 6TG is unknown. SOS is defined according to the international Ponte di Legno definition, fulfilling at least 3 of 5 criteria: (1) Hyperbilirubinemia, (2) unexplained thrombocytopenia (i.e., without concurrent neutropenia), (3) weight gain > 5.0%, (4) liver pain, and (5) ascites. Sonographic demonstration of compromised hepatic blood flow can support the diagnosis, but is frequently normal. In case of SOS in a patient in the experimental TEAM arm, that patient is taken off 6TG and treated according to the 6MP/MTX control arm. Any case of SOS should be registered in the ALLTogether1 online database within 24 h.

Nodular regenerative hepatotoxicity (NRH): This is a non-cirrhotic portal hypertension, which can be induced by thiopurine therapy. There are typically symptoms of portal hypertension (weakness, ascites, splenomegaly, esophageal varices) in a patient with little evidence of chronic liver disease. The diagnosis is confirmed by liver biopsy, showing absence of significant fibrosis and presence of nodularity usually best defined by reticulin staining. On superficial review, the liver biopsy may appear normal. NRH is usually accompanied by unexplained thrombocytopenia. Serum enzymes are generally normal or minimally elevated, although acute elevations in serum enzymes accompanied by SOS may precede the development of NRH. Jaundice is rare. Ultimately, NRH may lead to liver failure and need for liver transplantation. Among ALL patients, NRH has mostly been described with 6TG therapy, but it is very rare with 6MP therapy or low dose 6TG therapy (< 12.5 mg/m^2^). In case of NRH in a patient in the experimental TEAM arm, that patient is taken off 6TG and then treated according to the 6MP/MTX control arm. Any case of NRH should be registered in the ALLTogether1 online database within 24 h.

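### The two sections on secondary endpoints give contradictory competing-event rules, and the general rule wrongly counts non-fatal SOS, NRH and osteonecrosis as competing events

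*Protocol article*

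**What the plan says.** All references are to the protocol article.

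- **Analysis of endpoints**, second paragraph, treats the secondary endpoints together. They are "estimated using the Aalen-Johansen estimator", and "Differences for the randomized arms will be compared using" Gray's test. Patients without the event of interest are censored when last seen, and "the alternative secondary endpoints will be considered competing events". The following sentence gives overall survival its own method (Cox and Kaplan-Meier).
- **Secondary study endpoints** lists overall survival, the association of DFS with DNA-TG, relapse, SMN, "Cumulative incidence of SOS and NRH" and "Cumulative incidence of osteonecrosis". For relapse it adds: "Here death in first complete remission (DCR1) and SMN will be analyzed as competing events". For SMN it adds: "Here DCR1 and relapse will be analyzed as competing events". It names no competing events for SOS/NRH or osteonecrosis.
- **Organ toxicities during maintenance therapy** says of SOS in the experimental arm that "that patient is taken off 6TG and treated according to the 6MP/MTX control arm". **Withdrawal of individual subjects** keeps patients moved off TEAM for toxicity, SOS included, in the intention-to-treat analysis.
- **Temporary halt for reasons of subject safety** places SOS during therapy and most relapses and SMNs after it, and sets the acceptable SOS risk at 3%.

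**The concern.** A competing event is one after which the event of interest can no longer occur or no longer counts. SOS, NRH and osteonecrosis are not of that kind for relapse or SMN. By the protocol's own account, a patient with SOS continues maintenance, stays in the analysis set and remains at risk. The Aalen-Johansen estimator counts only the first event, so if a toxicity is coded as competing, any later relapse in that patient disappears from the relapse curve. The timing makes such losses possible, because SOS arises during therapy and most relapses come later.

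Two things are at stake. Relapse is the mechanism on which the DFS hypothesis rests, and its analysis is defined in two incompatible ways. The toxicity endpoints, among them the main 6TG-specific harm, are governed only by the over-broad rule. In an open-label trial such definitions should be unambiguous before outcome data are examined.

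**Working it through.** **1. The rules side by side**

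| Endpoint | Secondary study endpoints | Analysis of endpoints, as written | Result |
|---|---|---|---|
| Relapse | DCR1, SMN | all other listed endpoints, so also SOS/NRH and osteonecrosis | conflict |
| SMN | DCR1, relapse | the same | conflict |
| SOS/NRH | none named | all others, so also osteonecrosis | only the general rule |
| Osteonecrosis | none named | all others, so also SOS/NRH | only the general rule |

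**2. Effect on relapse incidence if the general rule were applied**

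The document states no relapse incidence for this analysis, so there is no figure to reproduce. The inputs are:

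- From Outcome assumptions (BCP-ALL): 5-year DFS 84% control and 91% target, so failure of 16% and 9%.
- Assumed split of those failures: relapse 14% and 7% (the 50% relapse reduction in the Abstract), DCR1 plus SMN 2% in each arm.
- From Maintenance therapy: weeks 37 to 108, so 71/52 ≈ 1.37 years in which toxicity arises.
- Assumed: constant hazards, toxicity independent of relapse, and toxicity rates varied over a range. The document gives no osteonecrosis rate and no toxicity rate by arm.

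Let L be the total hazard of relapse, DCR1 and SMN, r the relapse hazard, and q the toxicity hazard during maintenance. Then

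incidence = r × { [1 − e^(−(L+q)·1.37)]/(L+q) + e^(−(L+q)·1.37) × [1 − e^(−L·3.63)]/L }.

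Experimental arm at 3% toxicity:

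- L = −ln(0.91)/5 = 0.01886
- r = L × 7/9 = 0.01467
- q = −ln(0.97)/1.37 = 0.02223
- Incidence = 0.01467 × (1.332 + 0.9453 × 3.509) = 0.0682, against 0.0700 with q = 0. The loss is 2.6% of its value.

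Other cases by the same formula:

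| Toxicity, control / TEAM | Relapse, control | Relapse, TEAM | Difference (points) | Ratio |
|---|---|---|---|---|
| not a competing event | 14.0% | 7.0% | 7.0 | 0.500 |
| 0% / 3% | 14.0% | 6.8% | 7.2 | 0.487 |
| 5% / 5% | 13.4% | 6.7% | 6.7 | 0.500 |
| 5% / 8% | 13.4% | 6.5% | 6.9 | 0.486 |
| 10% / 10% | 12.8% | 6.4% | 6.4 | 0.500 |
| 5% / 15% | 13.4% | 6.1% | 7.3 | 0.455 |

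As a count, 778/2 = 389 TEAM patients × 3% ≈ 12 with SOS. At a later failure risk of 9% that loses 389 × 0.03 × 0.09 ≈ 1.1 relapses. At 16%, the control failure rate and so an upper bound, it is 1.9. The formula above gives 389 × (0.0700 − 0.0682) ≈ 0.7. So about one relapse, at most two.

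**3. Effect on the toxicity endpoints, where only the general rule applies**

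Take SOS at 3% and osteonecrosis at an assumed 10% over the same window, independent, ignoring other events. The incidence of SOS as first toxicity is

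[ln 0.97/(ln 0.97 + ln 0.90)] × (1 − 0.97 × 0.90) = 0.2243 × 0.127 = 2.85%, instead of 3.0%.

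At 5% osteonecrosis it is 0.3726 × 0.0785 = 2.92%. The shift is small, but it lowers the estimate of a harm that has a stated 3% limit.

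**The case against.** The strongest reply is that a definition attached to a named endpoint governs over a summary sentence. On that view the relapse and SMN analyses are already correctly defined, and the general sentence only abbreviates them. Overall survival is on the same list yet gets its own method, which suggests that the sentence was not meant for every listed item. This is a fair reading for relapse and SMN, but the document does not state it, and it does not help SOS/NRH and osteonecrosis, for which no specific definition exists.

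A reader might infer three stronger things that the document does not support:

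- **That relapse incidence will be underestimated in a way that flatters TEAM.** This needs the general rule to override the specific one, and also unequal toxicity. With equal rates the ratio stays at 0.50 and the absolute difference shrinks, because more control relapses are lost. The Discussion reports no link between MTX or 6MP metabolites and osteonecrosis, so an arm difference there has no stated basis. It also anticipates a low SOS/NRH risk; 3% is a limit, not a forecast.
- **That death has been left out.** Overall survival is on the list, so deaths are arguably covered, and DCR1 is named for relapse and SMN.
- **That Gray's test without the minimization factors is an error.** It is a standard secondary comparison, and adjusted models can be left to an analysis plan.

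**Conclusion.** The point stands as a contradiction between two stated rules, plus a wrong rule for the toxicity endpoints. It is not a matter of detail left to another document, because the over-broad rule is printed. Its numerical effect is modest. If applied to relapse, it would lower 5-year incidence by about 3% of its value at 3% toxicity and 9% at 10%. It would leave the arm ratio at 0.50 under equal toxicity and move it to about 0.49 under a 3-point TEAM excess. A 10-point excess would take the ratio to about 0.46, but nothing in the document suggests one. These figures rest on the assumed relapse split, constant hazards, independence and assumed toxicity rates.

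The primary DFS analysis is unaffected: relapse counts there whether or not a toxicity came first, and patients shifted off TEAM remain in it. Severity: should be fixed.

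**What to change.** In Analysis of endpoints, replace the general clause on competing events with endpoint-specific statements:

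1. Relapse: DCR1 and SMN compete. SMN: DCR1 and relapse compete. Both are as already printed under Secondary study endpoints.
2. SOS/NRH and osteonecrosis: DCR1 competes. State explicitly, for each, whether relapse and SMN are competing events or whether follow-up for the toxicity continues past them.
3. SOS, NRH and osteonecrosis are never competing events for relapse, for SMN or for one another.

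Gray's test can stay as it is. The cost is a few lines of wording. No change is needed to sample size or primary analysis, and none to data collection unless toxicity is to be followed past relapse or SMN, in which case the team should confirm that those data are captured.
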